### 2.3. Later PD randomisation

Patients who develop motor complications that are uncontrolled by LD (alone or in combination with either DA or MAOBI), and hence require the addition of another class of drug are eligible for the later disease randomisation.

[figure not shown]

**Question 3** will be addressed by comparison of arms 1 and 2 (COMTI or MAOBI) with arm 3 (DA).

**Question 4** will be addressed by comparison of arm 1 (COMTI) and arm 2 (MAOBI).

Patients who were already receiving a DA when uncontrolled motor complications arose are not eligible for the DA arm but can be randomised between COMTI and MAOBI. Patients who were receiving a MAOBI when uncontrolled motor complications arose, or for whom the clinician considers that MAOBI treatment is definitely contraindicated, are not eligible for the MAOBI arm but can be randomised between COMTI and DA.

[figure not shown]

N.B. Patients who have been entered into the early disease randomisation should be re-randomised into the later disease randomisation if motor complications develop that cannot be controlled by drug dose titration and/or addition of LD if on DA/MAOBI.

### 3. LARGE, SIMPLE TRIAL: MINIMAL EXTRA WORKLOAD

The differences between active agents are likely to be smaller than those between any one agent and a placebo control. Thus, larger numbers of patients will be required for the reliable detection, or reliable refutation, of any worthwhile differences between different classes of drugs. To make widespread participation from a large number of centres practicable, the PD MED trial procedures are 'streamlined', with minimal extra workload placed on participating clinicians, beyond that required to treat their patients. This is achieved by simple entry procedures (a single phone/fax call to the randomisation office), the use of standard, open-label treatment regimens, follow-up as in routine practice (with no additional hospital visits or tests to be performed above those done as part of standard care), minimising documentation, and largely patient-based evaluation of outcome (through postal questionnaires). This information will be supplemented by the use of national mortality records to ensure long-term follow-up. Regular newsletters will keep participants informed of trial progress, and regular meetings of collaborators will be held to address any problems encountered in the conduct of the study.

#### 3.1. Simple eligibility and randomisation based on "uncertainty"

There is disagreement on the extent to which the development of motor fluctuations and dyskinesia after long-term LD therapy is due to cumulative effects of LD or to progressive disease. LD-sparing therapy does appear to delay the onset of dyskinesia, but this needs to be weighed against the poorer symptomatic control, and an increase in other troublesome side-effects such as hallucinations. Because of the lack of reliable randomised evidence on which initial therapy is best, there is considerable divergence in clinical opinion and practice. At one end of the spectrum, some clinicians consider that the evidence for LD-sparing therapy is insufficient to justify use of the more expensive and clinically less effective new DAs. Such doctors, who are sceptical about LD toxicity, might consider using LD-sparing therapy only for younger patients for whom the potential for long-term toxicity is a more important consideration. Other clinicians believe that younger patients should be offered LD-sparing therapy on existing evidence but are uncertain whether more elderly patients should be offered LD or LD-sparing therapy. Still others would wish to consider either LD or LD-sparing therapy for their whole range of patients. Other factors, such as the level of disability of patients, are also potential determinants of the appropriateness of different Parkinson's treatment - and, again, there are divergent opinions. Similarly, some doctors are concerned about the safety of selegiline because of the UKPDRG Study and would wish to avoid using it. Others are sceptical about this evidence and believe that this inexpensive drug of proven effectiveness should not be discarded prematurely.

In view of these considerations, the PD MED trial adopts a pragmatic approach with eligibility based not on rigid entry criteria but on the "**uncertainty principle**". That is, if the doctor considers, for any reason, that there is a **definite indication** for, or a **definite contraindication** against, a particular class of PD drug, then the patient is not eligible for a randomisation including this class of drug (although the patient can still be randomised in one of the two-way randomisation options). If, on the other hand, the doctor is **substantially uncertain** which class of drug a particular patient should be offered, that patient is eligible to be randomised. In these circumstances randomisation is both scientifically and ethically preferable to the uninformative alternative of not randomising and treating patients in an ad hoc way outside of a study. Eligibility based on uncertainty has been used in many previous trials (e.g. the "ISIS" trials in acute MI, the MRC carotid endarterectomy trial, and the QUASAR colorectal cancer trial) and has been shown to simplify trial procedures and to facilitate large-scale recruitment of an appropriately heterogeneous group of patients.

#### 3.2. Open label treatment

Blinding of treatment allocation is not considered necessary in PD MED because the potential for subjectively biased assessment is small. There is no reason to expect that patients will have any prior beliefs that one treatment will be better than another (all patients in both randomisations receive active therapy - there are no placebo arms). Likewise the main outcome measures are well-validated, reproducible, patient-rated measures of disability and quality of life.

Moreover, the pragmatic, 'real life' design of the trial, which allows clinicians to choose which DA, MAOBI and COMTI to use, and to vary the dose as they see fit, has substantial advantages. The eventual results will be more clinically relevant, in that drug usage will reflect normal clinical

practice which involves frequent dose adjustments to achieve optimal symptom control. Another factor that precludes blinding is the cost of buying, encapsulating and distributing all the drugs for this long-term study, which would be prohibitive. Furthermore, patients with PD will normally obtain their prescriptions from their GPs. Trial procedures are simplified, treatments are given as they would be in normal clinical practice and administrative costs are greatly reduced with open treatment. The substantial advantages of simple, 'real life' procedures that will facilitate large-scale recruitment from many centres, enabling a uniquely large and therefore a uniquely reliable evaluation of the relative merits of different drugs to be undertaken, greatly outweigh the small possibility of assessment bias with open-label treatment.

## 4. OUTCOME MEASURES

### 4.1. Patient and carer outcomes

The primary outcomes will be the patient's self-evaluation of their functional status and quality of life (using the PDQ-39 questionnaire) and cost-effectiveness (EuroQoL EQ-5D).

Secondary endpoints will evaluate other aspects of functionality, and safety:

- Cognitive function (MMSE)
- Well being of carers (SF-36)
- Resource usage
- Toxicity and side-effects, including mortality rates
- Time to onset of motor complications (early disease randomisation only) and time to surgical intervention or start of apomorphine (later disease randomisation only)
- Capability in older people used in economic evaluation (ICECAP-O)
- Carer Experience Scale (CES)

**PDQ-39:** A clinically and socially meaningful outcome measure needs to address matters of most concern to the individual with PD. The PDQ-39 is a patient-completed questionnaire developed by qualitative in-depth interviews involving patients with PD. It includes items that reflect patients' concerns in relation to eight aspects of PD: mobility, activities of daily living, emotional well-being, stigma, social support, cognition, communication and bodily discomfort. The instrument has been extensively tested for validity, reproducibility and sensitivity to change in both clinic and population survey applications. For example, the instrument has high convergent and discriminant validity in relation to neurologists' assessments of PD severity using conventional clinical scores, such as Hoehn and Yahr, Columbia and UPDRS, and is sensitive to changes considered of importance to patients, but not identified by clinical ratings. It has been translated and used in most European, Australasian and North American countries and has been widely used as an outcome measure in trials of drugs, neurosurgery and nursing care packages.

**EuroQoL EQ-5D:** The main outcome measure for the economic evaluation will be the EuroQoL EQ-5D. Responses will be given valuations derived from published UK population tariffs and the mean number of quality adjusted life-years (QALYs) per patient and incremental QALYs will be calculated. The incremental cost per QALY will then be calculated. All parameters subject to uncertainty will be systematically varied in sensitivity analyses.

**ICECAP-O:** is a new measure of capability in older people for use in economic evaluation. Unlike most profile measures used in economic evaluations, the ICECAP-O focuses on wellbeing defined in a broader sense, rather than health. The measure covers attributes of wellbeing that were found to be important to older people in the UK. It will be evaluated to see if it provides an improved sensitivity in outcome measures for patients with PD compared to the EQ-5D.

**Cognitive function - Mini-Mental State Examination (MMSE):** About 10% of PD patients develop dementia. The trial aims to determine whether therapies prevent or decrease the decline of cognitive function - as measured by MMSE - in PD. MMSE is a well-established 30-point

measure of cognitive function in older people. It is easy to administer, shows good test/retest and inter-rater reliability and performs satisfactorily against more detailed measures of cognitive function. The MMSE is more sensitive than alternative measures at milder levels of cognitive impairment. MMSE score is influenced by sociodemographic status but this will even out in a large randomised study. Levels of 10 to 26 correspond to mild to moderate cognitive impairment in dementia. A score below 10 represents severe disabling dementia and is a milestone from which patients rarely recover.

### **Carers**

The primary carer should be in at least weekly contact with the patient, preferably co-resident, and should not be someone who is employed as a carer. If there is no suitable carer, or the carer chooses not to participate, the patient can still take part in PD MED.

**Carers' psychological well-being:** Little work has been done on the effect of anti-Parkinsonian drug prescription on carer attitudes, stress or physical and psychological morbidity. The person identified by the patient as their primary carer will be assessed by the SF-36, a well-validated measure of health status.

**Carer Experience Scale:** It is a new profile measure of the caring experience for use in economic evaluation. Unlike most profile measures used in economic evaluations, the CES focuses on 'care-related quality of life' rather than health-related quality of life, comprising attributes that are pertinent to unpaid carers.

**Side-effects of treatment:** The PDQ-39 includes items to assess self-rated severity of PD symptoms. In addition, potential side-effects of drugs, changes to drugs and institutional stays will be assessed by a patient-based instrument developed specifically for the study.

## **4.2. Resource usage**

**Direct medical costs:** An economic evaluation will be undertaken as part of the trial. Depending on the clinical results of the study, a cost minimisation study (no clinical difference between therapies) or cost-utility analysis (cost per incremental QALY gained) will be performed. Data will be collected from a sample of patients on the volume and type of resources used over the follow-up period. Information on medications, clinic visits, adverse events, hospitalisations and institutionalisation will be collected as an integrated part of the trial case record forms. A sub-sample of patients will be used to estimate the volume and opportunity costs of formal and informal care received by patients. Further details of hospitalisations (main reasons for admission, length of stay) will be collected from the relevant hospitals as required. In addition, patients will be asked at 12-month intervals to complete a simple (one A4 sheet) postal questionnaire covering GP consultations, physiotherapy out-patient visits, hospital stays and other health care resources used over the previous 12 months. All resources used will be costed using current unit costs derived from national statistics and participating centres, and a mean net cost per patient in each trial arm and incremental cost per patient with associated measures of variance will be calculated.

**Institutional care:** Progression of PD may lead to increased requirements for formal domiciliary or residential care as the limits of informal care are exceeded in some patients. Transitions to more intensive forms of care can be viewed both as outcome and as costs. The transitions to formal or paid inputs of care will impose costs either on the public sector or families. Public sector costs are likely to be borne initially by the NHS in terms of short term admissions (geriatrics, neurology), followed by individual needs assessment by the Local Authority Social Services (LASS), leading in turn to packages of domiciliary care and later, if and as appropriate, to placement in a residential care or nursing home. To the extent that PD therapies delay these transitions, they may reduce costs. The economic evaluation will adopt a societal perspective including informal and formal costs, i.e. those borne by the NHS and by LASS or privately by patients or their families.

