## **2. TRIAL DESIGN**

### **2.1. Separate randomisations in early and later disease**

PD MED is a large, simple, "real-life", randomised assessment of the relative cost-effectiveness of different classes of drugs for both early and later PD.

The four fundamental questions being addressed by two semi-factorial randomisations in this trial are:

1. Does early treatment with levodopa-sparing therapy (either a DA or a MAOBI) delay deterioration in quality of life compared to LD alone?
2. Which class of LD-sparing treatment is preferable (DA or MAOBI)?
3. For patients with motor complications uncontrolled by LD alone, should DDIs or DAs be added to LD?
4. If so, which class of DDI (COMTI or MAOBI) is preferable?

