## 7. SIZE OF DIFFERENCE TO BE MEASURABLE

### 7.1. Projected accrual

The PD MED study adopts a pragmatic approach to recruitment aiming to include, if possible, 1500 patients in the early disease randomisation and 1000 in the later disease randomisation. These numbers would give very high statistical power (i.e. over 90% power at  $p < 0.01$ ) to confirm, or refute, even small differences between the different classes of drugs and, should differences emerge, would also be enough to allow meaningful exploration of any differences in the size of benefit between different types of patient, between particular drugs within a class, or over time.

The minimum clinically meaningful difference used for sample-size calculations is 6 points on the PDQ-39 mobility scale. This 6-point difference is based on a study of patients attending neurology clinics with PD who completed the PDQ-39 at base-line and four months later and were also asked to complete 'transition questions' at follow-up. Patients who rated themselves as worse at follow-up, whether in terms of a transition item on physical function or an item on their PD generally, experienced a mean deterioration of 7 points on the PDQ-39 mobility scale. A 6-point change is used in PD MED because it translates more easily into meaningful categories, both of health states and health changes. The mobility scale has 10 items with 5 response categories (ranging from 'never' to 'always') and scores ('0' to '4') are transformed to produce a range 0-100. A 6-point change therefore results if a respondent changes three categories on one item, for example from 'being confined to the house - never' to 'being confined to the house - often'. The same change in score would also result from changing one response category - for example, from 'sometimes' to 'often' - on three of the ten items.

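### Section 4.2 lets the clinical result choose between cost-minimisation and cost-utility analysis, with no criterion, and so conflicts with the unconditional cost-per-QALY analysis in section 4.1

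*Protocol*

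**What the plan says.** Cost-effectiveness is the declared purpose of the trial. Section 2.1 calls it a "randomised assessment of the relative cost-effectiveness of different classes of drugs for both early and later PD". Section 4.1 places cost-effectiveness, measured through EQ-5D, beside PDQ-39 as a primary outcome, and adds: "The main outcome measure for the economic evaluation will be the EuroQoL EQ-5D". It then sets out the analysis: mean and incremental QALYs per patient, after which "The incremental cost per QALY will then be calculated". On uncertainty it says "All parameters subject to uncertainty will be systematically varied in sensitivity analyses". None of these statements is conditional.

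Section 4.2 does set a condition: "Depending on the clinical results of the study, a cost minimisation study (no clinical difference between therapies) or cost-utility analysis". It does not say which clinical result governs the choice, how an absence of difference would be established, or whether the choice is made once or separately for each of the four comparisons in section 7.2.

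The only effect size in the protocol is in section 7.1: "The minimum clinically meaningful difference used for sample-size calculations is 6 points on the PDQ-39 mobility scale". It is a difference to detect. It is not called an equivalence margin and is not linked to the economic analysis.

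**The concern.** If the cost-minimisation branch is taken, the analysis promised for a primary outcome gives way to a comparison of costs alone. That is valid only if the health benefits are known to be equal, and nothing in the protocol defines how equality would be shown. The sample size is built on detecting differences. Section 7.1 nevertheless says that the planned numbers can also refute small differences, and section 8.3 looks ahead to the cheaper drugs proving equally effective. In that setting a non-significant PDQ-39 comparison could easily be taken as the trigger.

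Three things are at stake. An imprecisely estimated QALY difference would be replaced by exactly zero. Its uncertainty would drop out of the decision, so the sensitivity analyses promised in section 4.1 could no longer cover it. And the method for a primary outcome would be chosen after the results are seen, possibly differently for different comparisons.

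**Working it through.** **1. The two rules side by side**

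| | Section 4.1 | Section 4.2 |
|---|---|---|
| Analysis | Incremental QALYs and cost per QALY | Cost-minimisation or cost per QALY |
| Condition | None | The clinical results |
| Criterion | Not needed | None given |

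Both can be followed only if the cost-minimisation branch is never used.

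**2. The protocol's own sample sizes (section 7.1)**

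Inputs: difference 6 points, SD 18.6, standardised difference 0.32. Sidedness is not stated; two-sided tests reproduce the figures. Formula: n per arm = 2 × ((z for alpha + z for power) / 0.32)².

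- 90% power, p<0.01: 2 × ((2.576 + 1.282) / 0.32)² = 291. The protocol says 300.
- 80% power, p<0.05: 2 × ((1.960 + 0.842) / 0.32)² = 154. The protocol says 155.

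The sizing arithmetic is sound for detecting a difference.

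**3. How often a real mobility difference would be non-significant**

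Formula (normal approximation): SE = 18.6 × √(1/n1 + 1/n2), and P(non-significant at 5%) ≈ Φ(1.96 − difference/SE). The illustrative true difference is 3 points, half the value used for sizing.

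| Patients | SE | 3/SE | P(non-significant), 5% |
|---|---|---|---|
| 155 v 155 | 2.113 | 1.420 | 71% |
| 300 v 300 | 1.519 | 1.975 | 49% |
| 500 v 500 | 1.176 | 2.550 | 28% |
| 1000 v 500 | 1.019 | 2.945 | 16% |

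The last row is the pooled comparison of DA or MAOBI with LD alone. It assumes that all 1500 early-disease patients are randomised three ways in equal numbers; section 2.2 also allows two-way randomisation. At p<0.01 with 300 per arm the figure is 73%. For a true difference of 6 points at 5%, it is 19% with 155 per arm and 2.3% with 300 per arm.

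**4. What a non-significant mobility result would exclude**

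The far confidence limit of a result that only just misses significance is 2 × z × SE.

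- 155 per arm, 95%: 2 × 1.96 × 2.113 = 8.3 points.
- 300 per arm, 95%: 2 × 1.96 × 1.519 = 5.95 points.
- 500 per arm, 95%: 2 × 1.96 × 1.176 = 4.6 points.
- 300 per arm, 99%: 2 × 2.576 × 1.519 = 7.8 points.

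A non-significant 5% result therefore excludes 6 mobility points at 300 per arm, by a hair, but not at 155 per arm, and not at the 1% level on which the figure of 300 rests.

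**5. From mobility to QALYs**

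Mobility is one of eight PDQ-39 dimensions. QALYs come from EQ-5D and survival, so a limit on mobility sets no limit on the QALY difference. The protocol gives no QALY SD. Assuming 0.15 to 0.35 per year, the 95% half-width with 300 per arm is 1.96 × SD × √(2/300), that is 0.024 to 0.056 QALY. Cost-minimisation would treat this interval as a single point at zero.

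**The case against.** Section 4.2 names no test and no p-value. A reader might infer that the plan treats a non-significant result as proof of equal benefit, but the text does not say so. Another reading is open: that the difference has been shown to be smaller than the 6-point value of section 7.1. With 300 or more per arm, a non-significant 5% result would roughly meet that reading on mobility. This stands, and it limits the point to a switch without a criterion. It does not remove the conflict with section 4.1, and it does not reach QALYs.

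The 3-point illustration is half of what the protocol regards as the minimum meaningful difference, and it is on the mobility scale. At 6 points and 300 per arm, non-significance at 5% is rare, and pooling lowers the 3-point figure to about 16%. This also stands; the percentages show the size of the ambiguity, not a bias in QALYs or costs.

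A reader might also infer that cost-minimisation hands the decision to the class with the cheapest drugs. Section 4.2 counts societal costs, including hospital, institutional and informal care, so a class with dearer drugs could still have the lower total cost. The direction of any bias is not shown.

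EQ-5D is collected throughout, and no sentence says that QALYs would go unreported under cost-minimisation. That is so, but a cost-minimisation analysis does not use them in its conclusion.

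Finally, operational detail commonly belongs in an analysis plan, which is not at hand. That covers the choice of estimation method. It does not cover a rule that the protocol itself states in two incompatible ways.

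**Conclusion.** The point holds as a conflict between two stated rules for a primary outcome. Section 4.1 promises cost per QALY without condition. Section 4.2 makes it depend on the clinical result and gives no endpoint, criterion or margin. A non-significant comparison could therefore be taken as equal benefit, and an uncertain QALY difference set to zero.

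The documents do not support the stronger statements that non-significance is the only possible trigger, or that the cheapest drugs must win.

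The illustrative size is a 71%, 49% or 28% chance of a non-significant result for a true 3-point mobility difference at 155, 300 or 500 per arm, and about 16% for 1000 against 500. These figures rest on SD 18.6, two-sided 5% tests and a normal approximation, and the last also on full three-way randomisation. The QALY half-widths rest on an assumed SD. The PDQ-39 analysis, the sample size and data collection are not affected.

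**What to change.** In section 4.2, delete the cost-minimisation branch. State that the cost-utility analysis will be done for each of the pre-specified comparisons in section 7.2 whatever the clinical result, and that incremental cost and incremental QALYs will be reported jointly with their sampling uncertainty. Section 4.1 can stay as it is. The choice between bootstrap, net-benefit regression and acceptability curves can be left to the analysis plan.

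The cost is about one sentence, best settled before the economic results are seen. EQ-5D and resource use are already scheduled in section 6.4 and Table 3, and section 4.1 already commits to the QALY calculation.
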